### Control

Current practice in most radiology departments is for GP examinations to be reported once the patient has left the department. Considerable variability exists across England in the time taken to report X-ray examinations (report turnaround time; RTAT). At Homerton University Hospital, all GP X-rays are reported during the next reporting session following examination, with a maximum RTAT of one working day. Patients who have a CXR suspicious for cancer are offered an appointment for a CT of the chest and upper abdomen via the radiology department secretary team, with the results sent to the referring GP and the cancer referrals office. Current practice is that if a suspected abnormality is identified by the radiographer who performs the CXR an urgent report (reporting radiographer or consultant radiologist) is arranged while the patient is still in the department. If the findings are suspicious for lung cancer the patent is offered a CT of the chest and abdomen. This protocol will continue throughout the study for the control reporting sessions.

### Outcome measures

The primary outcome is to test the impact of radiographer immediate reporting of GP CXRs, with immediate CT where appropriate, on time from performance of the CXR to treatment (with intermediate time points)/discharge for lung cancer.

Secondary outcome measures include:Measurement of the effect on the speed of the lung cancer pathway:
(i)6-and 12-month survival (lung cancer and all-cause)(ii)Number of emergency admissions for lung cancer(iii)Performance status at time of decision to treat(iv)Stage at diagnosis of lung cancer
Measurement of the effect of the pathway on efficiency including:
(i)The impact of immediate GP CXR reporting on the number of urgent respiratory cancer (2WW) referrals(ii)The accuracy and usefulness of radiographer CXR reporting in clinical practice(iii)The cost-effectiveness of radiographer reporting(iv)The influence of immediate GP CXR reporting, with immediate CT where appropriate, on the number of first 2WW appointments with all radiology results available
Measurement of the number of repeat CXRs performed in a timely fashion for suspected infectionThe effect of immediate reporting of GP CXRs on patient satisfaction

In addition to comparison as per randomisation within Homerton University Hospital, primary outcomes will be compared with a neighbouring hospital, Newham University Hospital.

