**Methods:**

A two-way comparative study that will compare the time to diagnosis of lung cancer for patients. Internal comparison will be made between those who receive an immediate radiographer report of a GP CXR compared to standard radiographer GP CXR reporting over a 12-month period. External comparison will be made with a similar, neighbouring hospital trust that does not have radiographer CXR reporting. Primary outcome is the effect on the speed of the lung cancer pathway (diagnosis of cancer or discharge). Secondary outcomes include the effect of the pathway on efficiency including the number of repeat CXRs performed in a timely fashion for suspected infection and the effect of immediate reporting of GP CXRs on patient satisfaction.

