**Discussion:**

The radioX trial will examine the hypothesis that immediate reporting of CXRs referred from GP reduces the time to diagnosis of lung cancer or discharge from the lung cancer pathway.

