### Trial design

A two-way comparative study that will compare the time to diagnosis of lung cancer for patients. Internal comparison will be made between those who receive an immediate radiographer report of a GP CXR compared to standard radiographer GP CXR reporting (Fig. 1). The intervention group will receive an immediate CXR report and be offered a CT for CXRs suspicious for cancer. The control group will have the CXR reported no later than next working day in line with current protocols. Key protocol elements are summarised in the SPIRIT (Standard Protocol Items: Recommendations for Interventional trials) 2013 Checklist [27] (Additional File 1) and Figure (Fig. 2).

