### Repeat chest X-ray for suspected infection

According to British Thoracic Society (BTS) guidance [33], patients who have a CXR that is suspicious for infection require a follow-up CXR 6 weeks later following antibiotic therapy to ensure resolution. The reporting radiographer will arrange the follow-up CXR at the time of the initial CXR report for the immediate reporting arm, and the patient will be asked to re-attend the radiology department in 6 weeks. This will be communicated in the CXR report.

For patients who have a CXR suspicious for infection in the standard care arm the recommendation for a follow-up CXR in 6 weeks will be included in the report conclusion. This will be requested by the general practitioner, as is current practice.

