### Statistical considerations

#### Sample size

For the primary endpoint in this pilot study, time to treatment decision for lung cancers, if we expect an 11-day advance in time to first treatment decision, with a standard deviation of 14 (previous audit data suggest this degree of variation), 26 cancers in each group will confer 80% power (two-sided testing, 5% significance level), for the internal randomised comparison. We expect around 50 cancers per year in Homerton University Hospital (HUH), so we will have adequate power for this difference. A reduction in time to diagnosis of 2 weeks was found to improve mortality of lung cancer patients so this difference could be clinically significant in the current pilot study [34]. If we anticipate a 12-day, instead of an 11-day advance in diagnosis, we would only need 22 in each arm, 44 cancers in all, for 80% power. For the external comparison, assuming that Newham University Hospital has a similar number of lung cancers per year, therefore, we would have close to 90% power for the same difference and standard deviation. If we also compare times to diagnosis for all persons referred to the pathway (lung cancer and non-lung cancer diagnoses), previous data suggest an average of 18 days and a standard deviation of 14. If the intervention improves this by 7 days on average, with a standard deviation of 15, we would need 73 subjects in each group referred to the pathway to achieve 80% power (two-sided testing, 5% significance level). Thus, both the internal and external comparisons will be adequately powered.

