## Discussion

The current study will determine the effect of immediate reporting of CXRs referred from GP, with immediate CT where appropriate, on the time to diagnosis of lung cancer. Although only one part of the patient pathway, immediate GP CXR reporting could positively impact lung cancer diagnosis and outcomes in at least three ways: firstly, by providing an immediate CXR report and initiating earlier further investigation including CT, the time to diagnosis will be shortened. There is debate within the academic literature as to the significance of this in terms of improvements in early survival times, performance status and reducing emergency admissions [34]. The current study will examine this, both with internal and external comparison. Secondly, the efficiency of the service may be improved by reducing the number of lung cancer pathway referrals through early provision of an alternative diagnosis, which in turn means less time for patient anxiety and distress. Thirdly, the proposal may release consultant radiologist time that can instead be used to interpret more complex cross-sectional imaging and support interventional procedures including lung biopsy. A reduction in average time to diagnosis for lung cancer will help centres meet the ambitious target of 90% of lung cancer patients definitively diagnosed within 28 days by 2020 [14].

Diagnostic capacity is a significant barrier to improved outcomes for cancer patients [14, 36], with prompt radiology reports a particular issue across England [15, 18].

The limitations of the current study include the fact that the intervention occurs only at a single clinical site at which the diagnostic aspect of the lung cancer pathway is already relatively streamlined. This is addressed by external comparison with a neighbouring hospital with similar patient characteristics and a comparable number of lung cancers diagnosed annually.

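### The primary endpoint is defined in several incompatible ways, the sample size fits only one of them, and the all-referred comparison selects patients after randomisation

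*Protocol article*

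**What the plan says.** The primary interval is described in five places in the protocol article.

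- Abstract, Methods: "Primary outcome is the effect on the speed of the lung cancer pathway (diagnosis of cancer or discharge".
- Abstract, Discussion: the hypothesis is that immediate reporting "reduces the time to diagnosis of lung cancer or discharge from the lung cancer pathway".
- Trial design: "A two-way comparative study that will compare the time to diagnosis of lung cancer for patients".
- Outcome measures: the effect "on time from performance of the CXR to treatment (with intermediate time points)/discharge for lung cancer". The section closes by referring to primary outcomes in the plural.
- Sample size: "For the primary endpoint in this pilot study, time to treatment decision for lung cancers", with the assumption "if we expect an 11-day advance in time to first treatment decision, with a standard deviation of 14". Later in the same paragraph, the 11-day and 12-day effects are described as gains in diagnosis.

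Sample size then adds a comparison of time to diagnosis among everyone referred to the pathway, with or without lung cancer. It concludes that both the internal and the external comparison are adequately powered.

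Outcome measures lists the number of urgent (2WW) referrals as a secondary outcome. The main Discussion expects a more efficient service from "reducing the number of lung cancer pathway referrals through early provision of an alternative diagnosis".

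**The concern.** Diagnosis, treatment decision, start of treatment and discharge are separate events on separate dates. An endpoint that can end in discharge takes in people without lung cancer; the powered endpoint does not. A reader cannot tell which interval, in whom, decides the trial. With about 25 cancers per arm, that choice could decide the result, and the text would allow it to be made after the data are seen. The stated 80% power would cover only one of the candidates.

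The all-referred comparison raises a second problem. Randomisation is of half-day sessions, so a patient's arm is set when the film is taken, and referral comes later. If immediate reporting changes who is referred, the referred patients in the two arms are no longer groups that randomisation made comparable, and a difference in mean time mixes a change in speed with a change in case mix.

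**Working it through.** **1. Definitions side by side**

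- Abstract (Methods and Discussion): ends at diagnosis or discharge; includes people without cancer, since discharge is an end event.
- Trial design: ends at diagnosis of lung cancer; cancers.
- Outcome measures: runs from the film to treatment or discharge; the intermediate points are not named and none is singled out.
- Sample size, primary endpoint: ends at first treatment decision; lung cancers only.
- Sample size, added comparison: ends at diagnosis; everyone referred.

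No two of these sections agree on both event and population, except the two parts of the abstract.

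**2. Reproducing the stated figures**

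Inputs, all from Sample size: differences of 11, 12 and 7 days; SDs of 14, 14 and 15; two-sided 5%; 80% power. Per group, n = 2 × (1.96 + 0.8416)² × (SD/difference)², and 2 × 2.8016² = 15.70.

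- 11 days, SD 14: 15.70 × (14/11)² = 25.4, so 26. Stated: 26.
- 12 days, SD 14: 15.70 × (14/12)² = 21.4, so 22. Stated: 22.
- 7 days, SD 15: 15.70 × (15/7)² = 72.1, so 73. Stated: 73.

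The external figure of close to 90% reproduces as one arm of 25 against 50 at the neighbouring hospital: SE = 14 × √(1/25 + 1/50) = 3.43; 11/3.43 − 1.96 = 1.25; power 0.894. The arithmetic is not at fault.

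**3. What the 26 per group does and does not cover**

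About 50 cancers a year, split equally between arms (equal split is my assumption), gives about 25 per arm.

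- Treatment decision in cancers, 11 days, SD 14: SE = 14 × √(2/25) = 3.96; 11/3.96 − 1.96 = 0.82; power 0.79.
- The all-referred effect of 7 days, SD 15, in groups of that size: SE = 15 × √(2/25) = 4.24; 7/4.24 − 1.96 = −0.31; power 0.38 (0.37 with the t distribution).

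The 38% shows that the cancer-sized target does not carry over to an endpoint covering everyone referred. It does not forecast the all-referred analysis, which would include more than the cancers.

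**4. Selection by referral**

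Suppose the intervention has no effect on speed but a share f of referrals, with mean time m, no longer occurs in the immediate arm. With the stated all-referred mean of 18 days, the remaining mean is (18 − f × m)/(1 − f), a shift of f × (18 − m)/(1 − f). The shift is positive if the lost referrals were quicker than average (a real gain is hidden), negative if they were slower (a gain is exaggerated), and zero if they were typical. The protocol gives neither f nor m.

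As an illustration only, assume gamma-distributed times with mean 18 and SD 14, and 5% to 20% of referrals lost from the shorter pathways. The immediate-arm mean then rises by 0.5 to 3.6 days, against a target effect of 7. Losing longer pathways would move it the other way.

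**The case against.** The article condenses a fuller protocol, and the intervals are successive points on one pathway. Outcome measures calls some of them intermediate, and Sample size does name one powered primary endpoint for the internal comparison. The added comparison is introduced conditionally, so the powered cancers-only test does not depend on referral. Control patients with suspicious films are also offered CT through radiology, and films flagged by the performing radiographer are reported at once in either arm. Any difference in early clearance is therefore one of degree.

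Much of this stands, and it limits the selection problem to the all-referred comparison. It does not remove the conflict over the endpoint: these are contradictory statements in the printed text, not details left to another document.

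Three stronger readings are tempting and are not supported.

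- A reader might infer that the clock starts differently by arm, because the six-week repeat film after suspected infection is arranged by the radiographer in the immediate arm, while in standard care "This will be requested by the general practitioner, as is current practice". But Outcome measures gives one start, the performance of the film, for all groups; Study setting assigns the study identifier to the patient; and nothing re-enters a repeat film as a new index film. The article does not say which film counts after a repeat, but such a rule may well stand in the full protocol.
- A reader might multiply end events by comparisons and quote a familywise error rate as if the tests were independent. They share patients and successive dates, so such a figure would overstate the inflation.
- A reader might take the selection bias to run in a known direction, or to affect the cancers-only test. The protocol settles no direction, and nowhere says that the intervention changes how many cancers are found.

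**Conclusion.** The point holds. The primary endpoint has conflicting end events and populations, and the 26 per group at 80% power belongs only to time to treatment decision in lung cancers. The protocol's own inputs require 73 per group for everyone referred. The 38% figure assumes an equal split of about 50 cancers and the stated 7-day effect with SD 15.

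The all-referred comparison is also exposed to selection after randomisation. That risk follows from the protocol's own expectation of fewer referrals, but its sign and size are unknown, and the range of 0.5 to 3.6 days rests wholly on assumed shares and an assumed distribution.

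**What to change.** - Name one primary end event and one population. Make both abstract statements, Trial design, Outcome measures and Sample size agree, and make the other intervals secondary. Which event to choose is for the investigators.
- Attach the matching sample size and power to that choice.
- State that patients stay in the arm of the session of their first eligible GP film and that time runs from that film.
- Either treat the all-referred comparison as secondary, acknowledging that referral follows randomisation, or, for the internal comparison, define its population by a criterion applied identically in both arms and not by referral. One example is an index film called suspicious by either the radiographer or the blinded consultant, since both reads are planned for every film. This should not be assumed to work for the external comparison, because the neighbouring hospital has no radiographers reporting chest films.

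The cost is mostly wording. The referral-free population would differ from the operational referral list, and some patients in it may never enter the pathway, so their end date needs a rule. The stated power may become less favourable: the 73 per group and the SD of 15 were derived for referred patients and would need to be recalculated.

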#### Data analysis

Times to diagnosis, treatment and other continuous outcomes will be compared using simple *t* tests. Categorical outcomes, such as proportions of emergency admissions, will be compared using Poisson regression. Survival will be compared using proportional hazards regression. Patient satisfaction will be recorded in categorical outcomes, and will be compared using non-parametric tests.

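### The primary outcome is defined in three incompatible ways, differing in end event and in population, and nothing in the protocol says which one decides the trial

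*Protocol article*

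**What the plan says.** Three places in the protocol article define a primary outcome.

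- **Abstract, Methods:** "Primary outcome is the effect on the speed of the lung cancer pathway (diagnosis of cancer or discharge" (the parenthesis closes there). The hypothesis in the abstract's Discussion agrees: immediate reporting "reduces the time to diagnosis of lung cancer or discharge from the lung cancer pathway".
- **Outcome measures:** "time from performance of the CXR to treatment (with intermediate time points)/discharge for lung cancer". The same section later refers to primary outcomes in the plural, for the comparison with the neighbouring hospital. It also uses "Measurement of the effect on the speed of the lung cancer pathway" as a heading over secondary outcomes such as survival and stage, although the abstract uses that concept for the primary.
- **Sample size:** "For the primary endpoint in this pilot study, time to treatment decision for lung cancers", tied to the internal randomised comparison.

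Two further places bear on the point. Trial design describes the study by diagnosis alone: "A two-way comparative study that will compare the time to diagnosis of lung cancer for patients". Within Sample size, the variant calculation begins "If we anticipate a 12-day, instead of an 11-day advance in diagnosis", although the 11-day figure was introduced as a gain in time to first treatment decision. That section then adds a separate calculation for time to diagnosis in everyone referred to the pathway, with or without cancer.

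Data analysis treats all times alike: "Times to diagnosis, treatment and other continuous outcomes will be compared using simple" t tests.

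**The concern.** The end event moves between diagnosis, treatment decision, treatment and discharge. The population moves with it. An endpoint that counts discharge takes in people found not to have cancer, whereas the Sample size section counts cancers only. The unnamed intermediate time points inside the primary outcome widen the choice further.

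The same data could therefore give a positive result on one version and a null result on another, and the protocol would not say which is the trial's answer. The Background section makes a larger multisite evaluation depend on positive results here, so what counts as positive has to be fixed beforehand. Two consequences follow: an inflated false-positive rate if the version can be chosen after the data are seen, and a headline result that might say nothing about cancer patients.

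**Working it through.** **1. The definitions side by side**

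| Section | End event | Population |
|---|---|---|
| Abstract, Methods (and hypothesis in Discussion) | Cancer diagnosis or pathway discharge | Discharge implies everyone on the pathway |
| Outcome measures | Treatment, with intermediate points, or discharge | Unclear: names lung cancer but includes discharge |
| Sample size | Treatment decision | Lung cancers only |

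Trial design (diagnosis of lung cancer) is a description rather than a labelled primary outcome, so it is not counted as a fourth version. It still has to agree with whichever version is kept.

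**2. Reproducing the stated sizes**

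Two-sample comparison of means, 1:1, two-sided 5%, 80% power:

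n per group = 2 × SD² × (1.96 + 0.8416)² / difference², where (1.96 + 0.8416)² = 7.849.

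- Treatment decision in cancers, 11 days, SD 14: 2 × 196 × 7.849 / 121 = 25.4, so 26. Matches.
- The 12-day variant, worded as diagnosis, same SD: 2 × 196 × 7.849 / 144 = 21.4, so 22. Matches.
- Diagnosis in all referred, 7 days, SD 15: 2 × 225 × 7.849 / 49 = 72.1, so 73. Matches.

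The arithmetic is sound; the labels are the problem. The second line is the first calculation with a different difference and a different endpoint name. The third sizes a related endpoint, but its text does not mention discharge. None of the three is for CXR to treatment or discharge. The section also gives no expected number of referred persons, so whether 73 per group is reachable cannot be checked.

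**3. False-positive rate if any version may be claimed**

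Three test statistics, jointly normal with a common correlation, no true effect, success if any exceeds 1.96 in absolute value (400,000 simulated draws):

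| Correlation (assumed) | Any of three positive |
|---|---|
| 0.9 | 8.4% |
| 0.8 | 9.8% |
| 0.5 | 12.5% |
| 0 (1 − 0.95³) | 14.3% |

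**4. A positive all-referred result without any cancer gain**

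If a fraction f of referred persons have cancer and their gain is zero, the non-cancer gain needed for a 7-day average is 7 / (1 − f). The documents do not give f, so these are assumed values:

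- f = 1/5: 7 / 0.8 = 8.75 days
- f = 1/3: 7 / 0.667 = 10.5 days
- f = 1/2: 7 / 0.5 = 14 days

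All three lie below the 18-day average the Sample size section quotes for everyone referred. The average for non-cancer patients alone is not given.

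**5. Keeping two primaries instead**

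With treatment decision in cancers and diagnosis in all referred as co-primaries, each at 2.5% (Bonferroni), the sizes become 31 cancers and 88 referred persons per group. The roughly 50 cancers expected, split 25/25 (assumed), would then give 70% power for 11 days, against 79% at 5%.

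**The case against.** The strongest defence is that the Sample size section, read alone, does name one primary endpoint and ties it to the internal randomised comparison. It introduces the all-referred calculation as an additional comparison. That is right, and it means one cannot say that no endpoint is ever singled out. It does not remove the conflict, because the abstract and the section headed Outcome measures name other endpoints. Condensing a protocol into an article explains omissions, not contradictory statements, and an analysis plan could not agree with all three.

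Several stronger readings are tempting, but the text does not support them.

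- *Only the treatment-decision version is powered.* It is not the only one: time to diagnosis in all referred is also sized, at 73 per group. What lacks a calculation is the Outcome measures wording.
- *Data analysis gives no test for the sized endpoint.* Its reference to other continuous outcomes covers time to treatment decision.
- *The immediate arm would score near zero days by construction, because diagnosis is dated at CT.* No section dates diagnosis at CT. The CT report serves as index diagnosis only for judging discordant CXR reports. Earlier CT is also part of the intervention under test.
- *Four primaries are in play, with a false-positive rate of 9% to 16%.* That counts a time-to-CT endpoint that no section names as primary.

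It is also fair to say that faster discharge of people without cancer is a stated aim, so an all-referred primary would be legitimate. That stands. The objection is to leaving the choice open, not to that endpoint. Finally, no section says that success on any one version would suffice, so the inflation is conditional on that reading.

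**Conclusion.** The inconsistency is established by reading alone: three definitions of the primary outcome, differing in end event and population and never reconciled, plus a slip from treatment decision to diagnosis inside the sample size calculation. The stated sizes of 26, 22 and 73 are arithmetically correct and are not in dispute.

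The 8% to 12% false-positive rate rests on two assumptions: that any one of the three versions could be claimed at an unadjusted 5%, and that their test statistics correlate equally at between 0.9 and 0.5. The possibility of an all-referred result driven wholly by non-cancer patients holds for each cancer fraction tried, but the fraction itself is assumed. The point must be fixed, because it decides which result answers the trial's question and the correction is one of wording.

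**What to change.** State one primary outcome in the same words in the abstract (Methods and the Discussion hypothesis), Trial design, Outcome measures and Sample size.

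The choice that leaves the stated sample size unchanged is the one the Sample size section already makes. Suggested wording: *The primary outcome is time from performance of the CXR to first treatment decision in patients with lung cancer, compared between sessions randomised to immediate and to standard reporting.* With it:

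- correct the 12-day sentence in Sample size so that it refers to treatment decision;
- list time to diagnosis, time to treatment, and diagnosis or discharge in all referred persons as secondary;
- put the reference to primary outcomes in the singular, and rename the secondary heading that repeats the abstract's primary.

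If the sponsor prefers diagnosis or discharge in all referred persons as the single primary, Sample size must name it as such and rest the power claim on a calculation for that endpoint. The 73 per group is a starting point, but it is worded for diagnosis and comes with no expected number of referrals.

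The cost is wording. No new data are needed and, under the first option, 26 per group stands. The other time points lose primary status, and the hypothesis as now written, which includes discharge, would be tested only as a secondary question.
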